### Sampling strategy and power calculations

We will use exhaustive convenience sampling to screen all eligible patients seen across two facilities over a 12-month period into the analysis cohort. Based on historical formative data of patient volume seen at these two facilities, and accounting for an expected 30% attrition rate, we conservatively expect that at least 1000 patients will be eligible for enrollment into the cohort.

With this conservative number of 1000 as our expected sample size based on this convenience sampling, we conducted power calculations to determine the statistical power to detect a change in the “at-goal” status. We calculate power based on a simplified design to compare paired proportions using a two-sided McNemar’s test with an 0.05 type I error (α) level. The primary outcome is the proportion of patients who achieve their NCD control target (“at-goal status”) after 12 months of being engaged in care. We used SAS version 9.4 (Cary, NC, USA) to estimate power to detect a 5% difference between discordant proportions; that is, proportions of patients whose “at-goal” status changed from “not at-goal” at baseline to “at-goal” at follow-up, and vice versa, in multiple scenarios where the total proportion of discordant patients ranged from 10 to 40% of all patients. Based on these assumptions, our power to detect a 5% difference in the discordant pairs is 69%, when the total discordant proportion is 40%, and the power is 99% when 10% of all patients are discordant.

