### Study setting

The study will take place in the Achham and Dolakha districts of Nepal across four municipalities. Following recent healthcare decentralization, Nepal’s 750 municipalities manage primary healthcare delivery. The intervention will be implemented in a step-wise fashion in coordination with municipal-level government authorities and study staff.

Achham is a remote, impoverished district of 260,000 people, with large migrant populations and a history of social disruption during the Nepali civil conflict [70–74]. Achham has one of the highest district-level under-5 mortality rates [75] and one of the lowest human development indices in the country [76]. The study implementers have been delivering some NCD-related care at the district-level Bayalpata Hospital and to communities within the hospital’s catchment population since 2008. Bayalpata Hospital serves approximately 90,000 outpatient and 3000 inpatient visits per year. CHW services include proactive case detection, care coordination, and counseling. The study will include a catchment population of approximately 50,000 in Achham across two municipalities.

The second district is Dolakha, one of the hardest hit districts in the 2015 earthquakes [77]. Nyaya Health Nepal’s work in Dolakha is based at Charikot Primary Health Care Center, which serves approximately 60,000 outpatients per year, with similar CHW services to those in Achham’s. The study will include a population of approximately 30,000 in Dolakha across two municipalities. Thus, the total expected study population will be 80,000.

Within the context of the public–private partnership between the government and Nyaya Health Nepal, no user fees are charged for any facility-based or community-based services, in either Achham or Dolakha, thereby mitigating financial access barriers to care delivery and study participation.

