### Data analysis

#### Analysis for Specific Aim 1: effectiveness

In order to assess the effectiveness of the intervention, as already described, the primary outcome will utilize disease-specific “at-goal” metrics for each of the three study diseases: hypertension, type II diabetes, and COPD. We hypothesize that the integrated intervention will lead to a 10% increase in the “at-goal” status of the combined disease cohorts, over a 12-month follow-up period.

We will use conditional multivariable logistic regression to assess patient outcomes at 12 months of follow-up, adjusting for potential confounding and/or effect modification by patients’ demographics (including age, sex, caste), municipality, district, mean distance to the hospital, and engagement in care (defined as number of facility-based and community-based encounters). We additionally hypothesize a 10% improvement in the status of each of the two secondary outcomes: tobacco and alcohol use, as measured by patient-reported outcomes presented in Table 1.

As a secondary analysis for Specific Aim 1, namely the time-varying nature of the outcomes, we will assess the longitudinal effect of the intervention, as measured in 3-monthly intervals, throughout the study period, compared to baseline statistics at the time of each village-cluster enrollment. Variables will be considered either nominal or continuous (linear effect) predictors, and the generalized linear model framework will be used to estimate effect of time-varying repeated-measure intervention implementation over the several steps of the wedged design. Differential impact from time of intervention will be evaluated with test of month × intervention interaction. Models will be fit using generalized estimating equations, for example, using SAS Proc Genmod, to calculate valid standard errors in the presence of repeated measures over time and possibly correlated outcomes at the municipality level. Assumptions of overdispersion or underdispersion will be examined closely, and an estimated scale parameter or negative binomial models will be used as needed.

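### The stated 69% to 99% power is for 1000 independent patients, so it is an upper bound if change varies between the four municipalities; separately, GEE clustered on four municipalities would not give valid standard errors

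*Protocol article*

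**What the plan says.** Four places in the protocol article bear on this.

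- **Study setting:** "The study will take place in the Achham and Dolakha districts of Nepal across four municipalities". There are two municipalities in each district.
- **Sampling strategy and power calculations:** the sample size is a forecast from patient volume at two facilities: "accounting for an expected 30% attrition rate, we conservatively expect that at least 1000 patients will be eligible for enrollment into the cohort". The method is given in these words: "We calculate power based on a simplified design to compare paired proportions using a two-sided McNemar". Alpha is set at 0.05. The aim is "to estimate power to detect a 5% difference between discordant proportions". Several scenarios were run, described as "in multiple scenarios where the total proportion of discordant patients ranged from 10 to 40% of all patients". The results are 69% power at 40% discordance and 99% at 10%. No ICC, design effect or number of clusters enters.
- **Analysis for Specific Aim 1: effectiveness, primary analysis:** a conditional multivariable logistic regression at 12 months. Municipality and district are among the factors adjusted for as possible confounders and/or effect modifiers. The hypothesis is a 10% rise in at-goal status.
- **Same section, secondary longitudinal analysis:** GEE models are to supply valid standard errors, allowing for repeated measures and for "possibly correlated outcomes at the municipality level".

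**The concern.** The power section counts every patient as an independent unit, while the analysis section allows that outcomes may be correlated within municipality. Only four municipalities exist, so each would hold about 250 patients. At that cluster size even a very small correlation inflates the variance noticeably.

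In a before-and-after comparison within patients, what matters is whether the change differs between municipalities. That is plausible here, because roll-out is step-wise and coordinated with municipal authorities. If change does vary, a test that allows for the variation has less power than stated, and one that ignores it rejects too often when the aim is to generalise beyond these four places.

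The second issue is the remedy that the protocol names. Robust GEE standard errors rely on many clusters. If municipality is the cluster, there are four.

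**Working it through.** **Inputs from the protocol.** N = 1000 pairs, two-sided α = 0.05, difference between the discordant proportions d = 0.05, total discordant proportion p = 0.10 to 0.40, four municipalities, hypothesised effect 10% (read here as 10 percentage points).

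**Assumptions not in the protocol.** Equal municipalities of 1000/4 = 250 patients, and an ICC of the within-patient change between municipalities of 0.001, 0.005 or 0.01.

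**Step 1: reproduce the stated power.** The normal approximation for McNemar's test is

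power = Φ[(d√N − 1.96√p) / √(p − d²)].

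- p = 0.40: (0.05 × 31.62 − 1.96 × 0.6325) / √0.3975 = (1.581 − 1.240) / 0.6305 = 0.54, so power is 70.6%. The exact test gives 69.0%, against 69% stated.
- p = 0.10: (1.581 − 0.620) / √0.0975 = 0.961 / 0.3122 = 3.08, so power is 99.9%. The exact test gives 99.9%, against 99% stated.

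Both figures reproduce with independent pairs, so they contain no allowance for clustering.

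**Step 2: allow for variation in change between municipalities.** Design effect = 1 + (250 − 1) × ICC. Replace N by N divided by the design effect in the same formula.

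| Assumed ICC | Design effect | Effective pairs | 5 points, 10% discordant | 5 points, 40% discordant | 10 points, 40% discordant |
|---|---|---|---|---|---|
| 0 | 1 | 1000 | 99.9% | 70.6% | 99.9% |
| 0.001 | 1.25 | 801 | 99.5% | 60.9% | 99.5% |
| 0.005 | 2.25 | 445 | 91.8% | 38.5% | 91.8% |
| 0.01 | 3.49 | 287 | 76.6% | 26.6% | 76.6% |

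The last column equals the first power column because doubling d and quadrupling p leaves the formula unchanged.

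At 5 points, power reaches 80% at an ICC of about 0.009 with 10% discordance and about 0.0024 with 20% discordance. At 40% discordance it is below 80% with no clustering at all.

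**Step 3: what these ICCs mean.** The between-municipality standard deviation of the change is √[ICC × (p − d²)]. At ICC 0.005 and d = 0.05 this is √(0.005 × 0.3975) = 4.5 percentage points at 40% discordance, and √(0.005 × 0.0975) = 2.2 points at 10%.

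**Step 4: sensitivity to equal sizes.** If patients split as the catchment populations do (50,000 and 30,000, each over two equal municipalities), the sizes are 312.5, 312.5, 187.5 and 187.5. The size-weighted mean is (2 × 312.5² + 2 × 187.5²) / 1000 = 265.6 instead of 250, so the design effects would be slightly larger.

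**Step 5: robust standard errors with four clusters.** With J equal clusters, the uncorrected sandwich variance of the mean change is (J − 1)/J times the usual between-cluster variance. A z-test at 1.96 therefore rejects when |t| with J − 1 degrees of freedom exceeds 1.96 × √((J − 1)/J). For J = 4 this is 1.96 × √0.75 = 1.697, and P(|t₃| > 1.697) = 18.8%. A simulation gave 18.7%. This step needs no ICC; it holds with no clustering at all.

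**The case against.** The strongest defence is that the correlation remark and the power calculation concern different analyses. The remark sits in the secondary longitudinal paragraph and speaks only of possible correlation. The power is for the primary 12-month paired comparison, whose model already lists municipality. Read as a fixed effect modifier, municipality makes the inference conditional on these four places, and the design effect does not apply. Stable differences in level between municipalities cancel within patients. Power was also computed for 5 points while the hypothesis is 10, enrolment is exhaustive rather than set by power, and the calculation is openly labelled simplified.

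Much of this stands. A reader might infer that the plan expects clustered outcomes and that the study therefore lacks its stated power. The protocol supports neither: it calls correlation possible, gives no ICC, and at an ICC of zero its figures are right. A reader might also treat the four municipalities as four observations and compute power on 3 degrees of freedom, but the protocol plans no such test.

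Two things remain.

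- If the conditional model conditions on the patient, as the pairing implies, a municipality main effect is constant within the patient and drops out. Only a municipality-by-time term captures differing change, and the wording, which leaves open confounding and/or effect modification, does not commit to one.
- Calling the design simplified does not tell the reader that ignoring positive correlation of change can only overstate power.

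The GEE cluster unit and any small-sample correction may be set in an analysis plan not seen here, so that part of the point is conditional too.

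**Conclusion.** The concern holds as an upper bound on power and a correction to the GEE, and no further. The 69% and 99% are correct for 1000 independent pairs, and they carry over to the study if change does not vary between municipalities or if the four are treated as fixed. Otherwise power is lower by an amount that the protocol does not allow anyone to fix. Over assumed ICCs of 0.001 to 0.01 the loss is slight to moderate at 10% discordance and large at 40%. For the hypothesised 10 points at 40% discordance, power stays above 90% up to an ICC of 0.005.

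The GEE point rests on two conditions: municipality is the cluster, and the robust z-test is uncorrected. Under them, the type I error is about 19% instead of 5%, and the promised valid standard errors are not delivered.

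**What to change.** **In Sampling strategy and power calculations:** state that the power is conditional on these four municipalities with patients independent within them, and show it over an assumed ICC range such as the table above, for both 5 and 10 points.

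**In Analysis for Specific Aim 1:**

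- Make the patient the GEE cluster and enter municipality and municipality-by-time as fixed effects. Define time as time since enrolment; a full set of municipality-by-calendar-period terms would absorb any roll-out step made at municipality level.
- Include municipality-by-time in the primary conditional model, and fix in advance how the four municipality-specific changes are averaged into the headline effect.
- State that inference is limited to these four municipalities.

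**Cost:** a less favourable printed power range, a few more model parameters, and explicitly narrower conclusions. No extra patients or data are needed.

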### Data collection

#### Quantitative data

Quantitative data for patient outcomes will be extracted from the facility-based EHR and the CHW’s mobile-phone application (Additional file 5), and will be used to assess Specific Aims 1 and 2. (Table 1) All implementation-related data for evaluating the performance of MLPs and CHWs (Table 1) will be collected by the responsible MLP and CHW supervisors in digitized checklists within the EHR and mobile-phone application. Access to protected health information will be controlled and defined by user access groups according to clinician status. Data to be analyzed will be extracted via secure data queries from the EHR system in an aggregate, partially de-identified form, with external researchers signing a data-sharing and use agreement prior to analysis. Cleaned, de-identified datasets will be made publicly available via a data repository.

Costing data for the intervention will be collected utilizing a “top-down” method, as described by the Joint Learning Network [85]. This method will document direct and indirect costs associated with the NCD care delivery intervention described here, and related administrative functions (including planning and administration; training; supervision and monitoring and evaluation; data management; and continuous surveillance) will be disaggregated. Full methodology of direct and indirect costs is provided by the Joint Learning Network [85], and will be utilized for this study. For the purposes of this pragmatic study, this methodology will be appropriate to estimate the additional marginal costs of the intervention (rather than cost-savings or secondary cost implications) as compared to general standard of care.

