		MLP visit fidelity	% of enrolled NCD patients with 100% of algorithm-indicated facility visits received, assessed during monthly physician supervision sessions, measured quarterly % of diagnostic, treatment, and counseling topics included at each session as dictated by the condition-specific algorithms, assessed during monthly physician supervision sessions, measured quarterly
		Implementation challenges	Exploratory and hypothesis-generating as revealed through FGDs and KIIs with CHWs, CHNs, MLPs, physicians, patients, and other relevant community stakeholders
	Maintenance	Total intervention cost	Cost of each intervention component and total costs using the Joint Learning Network costing methodology
		Intervention initiation costs	% breakdown of initial (one-time) costs for intervention (training, equipment, etc.)
		Intervention maintenance costs	% breakdown of maintenance (recurring) costs (ongoing training, personnel, materials, and other)
		Facility vs. community costs	% of costs of healthcare divided between facility level and community level
		Geographic cost variation	Characterization of variance in costs between village clusters and districts within the intervention catchment area
		Out-of-pocket patient costs	% costs of healthcare divided between facility level and community level
		Integrated intervention cost-effectiveness analysis	Pre/post-intervention marginal effectiveness for primary outcomes
		Cost per unit	Intervention cost per enrolled patient Intervention cost per capita Projected cost to scale intervention nationally, based on known incidence and prevalence of each condition

*CHN* community health nurse, *CHW* community health worker, *COPD* chronic obstructive pulmonary disease, *EHR* electronic health record, *FGD* focus group discussion, *GPS* Global Positioning System, *KII* key-informant interview, *MLP* mid-level practitioner, *NCD* Noncommunicable disease, *RE-AIM* Reach, Effectiveness, Adoption, Implementation, Maintenance

**Table 2 Tab2:** Clinical definitions of “at-goal” status for each intervention condition

Noncommunicable disease	Management metric	“At-goal” definition
Type II diabetes mellitus	Hemoglobin A1c OR fasting blood sugar	Hemoglobin A1c < 7.5 OR fasting blood sugar < 130 mg/dl^a^
Hypertension	Blood pressure	Blood pressure < 130/80 mmHg or patient-tailored goal per risk stratification^b^
Chronic obstructive pulmonary disease	Exacerbation status	≤ 1/3 Anthonisen criteria^c^

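### Top-down costing is called appropriate for the intervention's additional marginal cost, but it gives an average allocated cost, and no standard-care cost is described to subtract from it

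*Protocol article*

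**What the plan says.** The costing paragraph is in the protocol article under Data collection, Quantitative data. It names the method: "Costing data for the intervention will be collected utilizing a “top-down” method, as described by the Joint Learning Network". It gives the scope: "This method will document direct and indirect costs associated with the NCD care delivery intervention described here". Administrative functions such as training, supervision and data management are to be shown separately. It then states what the method is good for: "this methodology will be appropriate to estimate the additional marginal costs of the intervention". A parenthesis sets this apart from savings and secondary cost effects, and the sentence ends "as compared to general standard of care". The full methodology is left to the cited source.

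Table 1 (Study outcomes, Maintenance rows) lists the metrics that use these costs:
- total cost: "Cost of each intervention component and total costs using the Joint Learning Network costing methodology";
- cost-effectiveness: "Pre/post-intervention marginal effectiveness for primary outcomes";
- unit costs per enrolled patient and per capita, and "Projected cost to scale intervention nationally, based on known incidence and prevalence of each condition";
- geographic variation: "Characterization of variance in costs between village clusters and districts within the intervention catchment area".

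Analysis for Specific Aim 2 names the same methodology for intervention costs and says the results are meant to inform planners and policy-makers about possible scale-up.

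Three other sections bear on the point. Study setting says some NCD care has been delivered at the Achham hospital and in its catchment since 2008, and describes CHW services in both districts. Study implementers says the study builds on a delivery network already in place. Study design says there is no control group and that no data from other sources exist before the study starts.

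**The concern.** Top-down costing starts from an expenditure total and divides it over outputs. What comes out is an average that includes whatever shared cost was in the total. The article claims something different: the cost added by the intervention relative to standard care. That is a with-minus-without quantity. It needs either a total that contains only added cost, or a measured standard-care cost to take away.

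The consequence is a label that may not fit its number. If existing staff time, facility running costs or administration are allocated to the intervention, cost per patient is too high as a measure of what the intervention adds. The cost-effectiveness metric would then set a full cost against a change in outcome from baseline. Numerator and denominator would answer different questions. The national projection would start from the same unit cost.

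**Working it through.** The article states no cost figure, so there is nothing to reproduce. The check sets the sections side by side and then uses a cost identity.

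**Step 1: the two conditions under which the claim would be true.**

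| Condition | What the article shows |
|---|---|
| No shared, pre-existing cost is allocated | Indirect costs are included (Quantitative data). The study builds on an existing delivery network (Study implementers), with NCD care in Achham since 2008 and CHW services in both districts (Study setting). No rule for excluding shared cost is given. |
| Standard-care cost is measured and subtracted | No costing of standard care is described. There is no control group and no earlier data from other sources (Study design). Deployment began in July 2018, and enrolment is expected from February 2020 (Trial status). |

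Neither condition is shown to be met.

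**Step 2: size of the discrepancy.** Let A be the cost added by the intervention and H the allocated cost that would be incurred anyway, whether overhead or existing staff time. The top-down total is T = A + H. With s = H/T, A = (1 − s)T, so

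T/A = 1/(1 − s).

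The article does not give s. Over an assumed range:

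| s | T/A |
|---|---|
| 0 | 1/1.00 = 1.00 |
| 10% | 1/0.90 = 1.11 |
| 25% | 1/0.75 = 1.33 |
| 50% | 1/0.50 = 2.00 |

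**Step 3: where the factor goes.** For n patients, the reported cost per patient is T/n and the additional cost per patient is A/n, a ratio of 1/(1 − s). For a change in outcome E, the reported cost per unit of effect is T/E against A/E, again 1/(1 − s). A national projection that multiplies unit cost by the number of cases starts with the same factor. What has to be added at new sites is a separate item, so the net direction of error in the projection is not fixed.

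**Step 4: geographic variation (conditional).** Suppose cost per patient truly varies between clusters of one facility with a coefficient of variation (CV) of 0.30 (assumed), and a share a of the cost is allocated equally per patient while the rest is traced. The CV shown is (1 − a) × 0.30:

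- a = 0: 0.30
- a = 25%: 0.75 × 0.30 = 0.225
- a = 50%: 0.50 × 0.30 = 0.15
- a = 100%: 0

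With a visit key whose own CV is 0.20 and which is unrelated to true cost (both assumed), the key's share of the variance shown is (0.20a)² / [(0.20a)² + (0.30(1 − a))²]. At a = 25% this is 0.0025/(0.0025 + 0.050625) = 5%. At a = 50% it is 0.01/(0.01 + 0.0225) = 31%. At a = 75% it is 0.0225/(0.0225 + 0.005625) = 80%. The distortion is slight when little is allocated and dominant only when most is.

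**The case against.** The strongest reply is that marginal is used loosely here. The sentence contrasts it with savings and secondary effects and compares it with standard care, so it probably means incremental programme cost, not the cost of one more patient. The object costed is the NCD intervention, not the hospital. That reading is fair, but it does not rescue the statement. Incremental cost also needs a with-minus-without contrast, and shared cost that would be incurred anyway still has to be left out or subtracted.

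A second reply is that the cited manual may deal with shared costs or add bottom-up steps, and that an article may leave such detail to its source. This stands as a limit. The manual is not at hand, so one cannot say that overhead will in fact be included, or how much. What can be said is that the article's flat statement of appropriateness has no support in what it describes.

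A third reply is that much of the remedy is already planned: administrative functions are shown separately, and Table 1 splits cost by component, by one-time versus recurring, and by facility versus community. That is true and makes the fix cheap. None of these splits separates added from pre-existing cost.

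Two stronger readings are tempting and should not be adopted:

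- A reader might infer that the plan declares the method fit for differences between village clusters, or that the geographic row would mostly report the allocation key. The costing paragraph does not mention clusters; the link comes only from joining Table 1 to Analysis for Specific Aim 2. No key or allocated share is given, direct costs are documented, and CHW cost could be traced to clusters. Differences between districts stay observable, because each has its own facility.
- A reader might try to size the overhead from the outpatient volumes in Study setting. The Achham figure counts visits and the Dolakha figure counts outpatients, so their sum is not a sound denominator, and no visit rate per study patient is given.

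**Conclusion.** The point holds for the marginal-cost statement. As described, the method gives an average allocated cost, and the article shows neither of the two conditions that would make this equal to the additional cost over standard care. The overstatement is 1/(1 − s), from none at s = 0 to twofold at s = 50%. The range for s is an assumption, and zero cannot be excluded.

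The effect is confined to the Maintenance metrics of Specific Aim 2: cost per patient and per capita, cost-effectiveness and the national projection. The primary outcome, its analysis and the power calculation are untouched. The change is still worth making, because these are the figures meant for decisions on scale-up. The cluster point is secondary and applies only to whatever part of the cost is allocated by a per-patient or per-visit key.

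**What to change.** 1. Label the top-down result as average full cost, and withdraw the statement that it estimates additional marginal cost.
2. Report an additional cost next to it, made up only of items and staff time that the intervention adds. For CHWs, count only time beyond the services they already provided. The functions that the costing paragraph already shows separately (training, supervision, data management and so on) are the starting point.
3. Use the additional cost, plus any capacity that would have to be added, for the marginal, cost-effectiveness and scale-up figures.
4. For the geographic variation row, trace CHW and supervision cost to village clusters from logged visits where possible, and state which part remains allocated and by what key.

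The cost is a change of wording in the costing paragraph, some extra costing work (mainly to separate added from existing staff time) and two cost figures to explain to readers.
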